### Procedures

Following referral (health care provider or self-referral), a member of the trial team contacts the caregiver via their preferred method (ie, email, phone call, or text message) to describe the PA intervention and trial, ascertain interest, confirm eligibility, and share the link to the participant consent or assent, and caregiver consent forms via REDCap. Once consent (or assent, as appropriate) is provided by the patient (henceforth referred to as the participant) and caregiver, the participant is scheduled for a baseline (week 0) assessment, which includes the collection of the participant’s device-measured PA through a 7-day Fitbit (Google LLC) wear period and tracking log. Caregivers also complete a questionnaire covering personal and medical information, and participants and caregivers complete a series of questionnaires via REDCap assessing participant- and caregiver-reported PA as well as the participant’s quality of life, symptoms, cognition, and resource use. Participants additionally complete a physical assessment via videoconference, measuring aerobic endurance, lower body flexibility, shoulder flexion range of motion, balance, and functional mobility. Once baseline assessments are completed, participants are matched with an exercise professional and begin the 12-week, individualized, 1:1 PA intervention. Following the PA intervention, participants and caregivers complete the same assessments as at baseline (with the exception of personal and medical information, which is collected only at baseline) and are invited to complete a postintervention interview via videoconference. At 6- (week 24) and 12-month (week 52) follow-up time points, participants complete the same assessments as at baseline (week 0) and postintervention (week 12), with the exceptions of personal and medical information, which is collected only at baseline, and the interview, which is conducted only postintervention. To enhance data completeness, notifications of assessments are sent via REDCap, and reminders are sent every 3 days for up to 2 weeks if assessments are not completed at baseline, postintervention, and follow-up time points. See Figure 1 for the CONSORT diagram.

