The resulting 12-week PA intervention, delivered via videoconference, includes sessions offered 3 times per week for 15-45 minutes and incorporates a combination of aerobic, resistance, balance, core, and flexibility exercises. Videoconference delivery allows participants to join whether they are at home or in the hospital. The intervention is tailored for each participant based on the frequency (ie, how often each exercise is completed and the number of PA sessions per week), intensity (ie, the difficulty of exercises or PA sessions), time (ie, duration of each exercise and each PA session), and type of exercise (ie, aerobic, resistance, balance, core, and flexibility). Each aspect of the intervention is modified based on participants’ needs, preferences, medical factors, age, and abilities, including how they are feeling and managing treatment-related side effects, their treatment schedules, and other considerations (eg, school or extracurricular commitments). PA sessions are provided regardless of whether participants are in the hospital or at home. Select behavior change techniques (eg, goal setting, feedback and monitoring, social support, self-monitoring) are embedded within PA sessions and discussed in an age-appropriate manner. Behavior change topics are also selected based on participant choice and ongoing conversations throughout the PA sessions. As noted above, participant autonomy is prioritized throughout. See Multimedia Appendix 2 for an overview of the PA intervention. Of note, caregivers are required to be present for each PA session, either at home or in the same room as the participant, depending on the participant’s age, functional characteristics, and preferences (see the “Safety” section). If caregivers wish, they may participate in the PA sessions after completing the Get Active Questionnaire to ensure readiness and safety for engaging in PA, although the primary focus remains on the participant [78].

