### Data Collection

#### Assessment Timeline and Data Collection

As described above, assessments occur at baseline (week 0), postintervention (week 12), and 6- (week 24) and 12-month (week 52) follow-ups. See Table 1 for an overview of outcome measures and time points. Following the RE-AIM framework, multiple types of information are collected.

**Table 1 table1:** Outcome measures and time points.

Reach (throughout)	Effectiveness (weeks 0, 12, 24, and 52)	Adoption (throughout)	Implementation (throughout)	Maintenance (weeks 12, 24, and 52)
Referral rate (numbers and sources) Number of participants excluded and reasons for exclusion Participation rate (number of participants consenting to participate divided by the number of eligible individuals referred) Personal and medical information (ie, sex, gender, and other factors [eg, age, cancer diagnosis, sexual orientation, race/ethnicity, cultural background, and socioeconomic status]) of participating participants and caregivers (collected through caregiver-reported outcomes at baseline only) Proportion of participants from rural versus urban locations	Device-measured PA^a^ levels Participant and caregiver questionnaires (PA, quality of life, symptoms, cognitive outcomes, and resource use) Assessments of physical function (aerobic endurance, lower body flexibility, shoulder flexion range of motion, balance, and functional mobility) Interviews with participants and caregivers to explore the benefits of the PA intervention (at week 12 only) Resource use Direct and indirect costs (costs of intervention delivery and trial management)	Sources of referral Differences in referrals across referring sites	Trial retention Adherence to the PA intervention Percentage of missing data Interviews with participants and caregivers to explore their perceptions of feasibility (at week 12 only) Intervention delivery time and cost Trial delivery time and cost Expertise of exercise professionals PA session fidelity Adverse events (safety)	PA levels at 6- and 12-month follow-ups PA referral into community programs Access/use of maintenance offerings PA referral implementation

^a^PA: physical activity.

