##### Participant and Caregiver Questionnaires (Week 0, Week 12, Week 24, and Week 52)

*Personal and medical information* is collected at baseline (week 0) from both participants and caregivers to describe their characteristics. This includes participants’ biological sex, gender, race, ethnicity, location, age, diagnosis, and year of diagnosis, as well as caregivers’ highest level of education, employment status, and annual household income. The questionnaire was developed by the trial team.

*Self-reported PA* at weeks 0, 12, 24, and 52 is assessed using a modified version of the Godin-Shephard Leisure-Time Exercise Questionnaire (m-GLTEQ) to capture frequency and duration of aerobic, resistance, flexibility, and balance training [90]. Participants complete the m-GLTEQ for themselves, regardless of age, and caregivers complete the m-GLTEQ based on both their own PA and their child’s PA behavior. Specifically, participants and caregivers report the number of times per week they (and, in the case of caregivers, both themselves and their child) engage in mild, moderate, and strenuous PA during leisure time for a minimum of 10 minutes. At baseline, they also report PA levels before their (or their child’s) cancer diagnosis, and at all other time points, they report PA over the past month. The m-GLTEQ is scored by calculating the total amount of PA (time × intensity) for each intensity and type of activity and summing the totals. Intensity is weighted using metabolic equivalents of 3, 5, and 9 for light, moderate, and strenuous PA, respectively. Higher scores indicate greater PA behavior. Reports will include total moderate-to-vigorous PA as well as total PA. The m-GLTEQ has demonstrated high reliability and validity in pediatric populations with cancer [91,92].

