*Cognitive executive functioning* at weeks 0, 12, 24, and 52 is assessed by caregivers using the Behavior Rating Inventory of Executive Function, Second Edition (BRIEF-2) [96]. The parent proxy report form is used for all children and adolescents [97]. The BRIEF-2 includes 9 items covering major areas of executive function—behavior, emotion, and cognitive regulation—scored on a 3-point scale: 1 (never), 2 (sometimes), and 3 (often). Caregivers indicate how often their child has experienced each problem behavior over the past 6 months. Raw scores are calculated and summed to generate a score for each subscale. Additional scoring is applied for the inconsistency, negativity, and infrequency scales. The t scores and percentiles are also calculated for each raw scale score, and 90% CIs are computed to estimate the measurement error associated with the clinical scale, index, or t scores. Higher scores indicate greater cognitive impairment. The BRIEF-2 has been used with pediatric participants with cancer [98] and has demonstrated reliability and validity in this population 94.

*Resource use* at weeks 0, 12, 24, and 52 is assessed by caregivers using a modified version of the Pathways in Autism Spectrum Disorder, Phase III Resource Use Questionnaire for Adolescents (RUQ-A; November 30, 2016) [99]. Items have been adapted to the context of this trial and population. The modified RUQ-A assesses 7 types of resources that participants may use: (1) school; (2) mental health and psychological interventions; (3) rehabilitative services (eg, occupational therapy, physiotherapy); (4) child-focused recreational activities; (5) medications; (6) additional services; and (7) caregiver time associated with treatment and care. Caregivers are asked to indicate the frequency of use and costs associated with each resource their child accessed over the past 3 months. A final open-ended question allows caregivers to report any additional resources and associated costs not captured in the listed categories. The RUQ-A is not scored, and information on validity, interrater and test-retest reliability, and responsiveness is not summarized or statistically reported [99]. The RUQ-A is flexible, allowing questions to be adapted for the population of interest [99]. Although the RUQ-A has previously been used with caregivers of children with autism [99], to our knowledge, this is the first adaptation of the modified RUQ-A for pediatric participants with cancer.

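### The BRIEF-2 asks about 6 months, so about half of its week-12 window precedes baseline; week 24 versus week 0 should be the main cognitive contrast

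*Protocol article*

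**What the plan says.** **BRIEF-2.** Under Participant and Caregiver Questionnaires, the cognitive measure is a caregiver rating on a never/sometimes/often scale at weeks 0, 12, 24 and 52: "Caregivers indicate how often their child has experienced each problem behavior over the past 6 months". No shorter recall is given for any visit. Under Assessment Timeline and Data Collection, "assessments occur at baseline (week 0), postintervention (week 12), and 6- (week 24) and 12-month (week 52) follow-ups", so the article itself equates 6 months with week 24.

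**Timing.** Under Procedures, "Once baseline assessments are completed, participants are matched with an exercise professional and begin the 12-week, individualized, 1:1 PA intervention", and "Following the PA intervention, participants and caregivers complete the same assessments as at baseline". The same section allows late completion: "reminders are sent every 3 days for up to 2 weeks if assessments are not completed at baseline, postintervention, and follow-up time points".

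**m-GLTEQ.** Baseline includes a report of activity before diagnosis; "at all other time points, they report PA over the past month". The form covers aerobic, resistance, flexibility and balance training in leisure time, in bouts of 10 minutes or more. The programme "includes sessions offered 3 times per week for 15-45 minutes", with much the same content (The Intervention). The Maintenance section uses later m-GLTEQ reports to explore whether activity is sustained.

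**Analysis.** Data Analysis first planned mixed models of change over time. Because recruitment is far below target, it now expects to emphasise individual trajectories. It does not say which visit carries the BRIEF-2 comparison. The Limitations section mentions neither recall window.

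**The concern.** A pre-post contrast needs a post rating that describes time after the start of treatment. At week 12 a 6-month recall cannot do that for a programme that began 12 weeks earlier. The two ratings share a block of weeks in which no child had started the programme, and this pulls their difference toward zero. Other questionnaires do not have this problem at week 12: the symptom tool asks about the past day and the resource-use form about the past 3 months.

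Cognitive function is a named secondary effectiveness outcome. There is no control group and the sample is small (16 completers and 1 child still in the programme as of October 2025). A flat week-12 result could easily be reported as no cognitive effect when the instrument was only partly looking at the programme.

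The m-GLTEQ raises the reverse question. Its week-12 month falls mainly or wholly inside the programme, so some reported activity may be the sessions. A lower week-24 report could then partly reflect that the sessions had ended. The primary outcome, the 7-day Fitbit step count, is scheduled after the programme and is not affected.

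**Working it through.** The plan states no figure to reproduce, so this is window arithmetic.

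**Inputs.** Recall window W: 6 calendar months = 365.25/2/7 = 26.09 weeks, or 24 weeks on the article's own convention. Time of the post rating t: 12 weeks after the start, or up to 14 if completion takes the full 2 weeks of reminders. Week 0 is taken as both baseline and programme start.

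**Share of the week-12 window before baseline** = (W − t)/W:

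| W (weeks) | t = 12 | t = 14 |
|---|---|---|
| 26.09 | 14.09/26.09 = 54% | 12.09/26.09 = 46% |
| 24 | 12/24 = 50% | 10/24 = 42% |

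The baseline rating covers the W weeks up to week 0, so all of these weeks were already rated.

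**Visible effect at week 12, if the window is weighted evenly.**
- Immediate full effect: t/W. This runs from 12/26.09 = 46% to 14/24 = 58%.
- Effect growing linearly over 12 weeks and then held: (6 + t − 12)/W. This runs from 6/26.09 = 23% to 8/24 = 33% of its final size.

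**Week 24 for comparison (completed on time).** The window starts at 24 − 26.09 = −2.09 weeks, or at 0. The pre-baseline share is 2.09/26.09 = 8%, or none. The window holds 12 programme weeks and 12 later weeks. Under even weighting:
- An immediate, lasting effect shows at 24/26.09 = 92% to 24/24 = 100%.
- An effect that grows linearly and then lasts shows at (6 + 12)/26.09 = 69% to 18/24 = 75%.
- An immediate effect that vanishes when the programme ends shows at only 12/26.09 = 46% to 12/24 = 50%, no better than week 12.

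**Week 52.** The window starts at week 52 − 26.09 = 25.9, or week 28, and so lies wholly after the programme.

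**m-GLTEQ at week 12.** A month is 4 to 4.35 weeks. Completed on time, it lies inside the programme and holds up to 3 × 4 = 12 to 3 × 4.35 = 13 sessions. Completed 2 weeks late, it holds up to 3 × 2 = 6 to 3 × 2.35 = 7. Full attendance gives 3 × 15 = 45 to 3 × 45 = 135 min/week in programme weeks. That is 135–405 MET-min/week at the light weight of 3, or 225–675 at the moderate weight of 5. These are ceilings, because session frequency, length and intensity are tailored to the child.

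**The case against.** **On the BRIEF-2.** A reader might infer that the week-12 score mostly describes the time before baseline. The documents do not support that. A majority appears only with calendar months and completion near week 12; the article's own convention gives exactly half, and late completion gives less. A reader might also treat 46% as an upper limit on the visible effect. It is not one: it assumes even weighting, which the article does not state, and if recent behaviour counts for more, the dilution is smaller. Moreover, the article never names week 12 as the main BRIEF-2 contrast, the outcome is secondary, and the authors promise cautious interpretation. All of this stands. It limits the size of the problem but not its direction, and nothing in the article corrects for the overlap.

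**On the m-GLTEQ.** A reader might infer that the questionnaire does count the sessions, that the week-12 result is therefore biased toward benefit, that it will conflict with the Fitbit, or that a week-24 fall is purely mechanical. None of these is established. The article neither includes nor excludes the sessions, and its restriction to leisure time leaves the choice to the respondent; the questionnaire's own instructions are not shown. Sessions are physical activity, so a total that includes them is a legitimate outcome, and the article nowhere says that out-of-session activity is the target. Sessions may also displace other activity. Subtracting session minutes for everyone would over-correct for families who never counted them. What remains is that responses can include sessions, and that the two activity measures describe different periods and may diverge for that reason.

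**Conclusion.** The BRIEF-2 point holds: about half of the week-12 window (42–54%) precedes baseline and duplicates time already rated, so the week 0 to week 12 change is diluted toward no change. The window share needs only the stated recall, the stated schedule and the range of delay. The size of the dilution (46–58% of an immediate effect visible, 23–33% of a linearly growing one) additionally assumes even weighting by caregivers.

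The already scheduled week-24 rating largely avoids the overlap. Its advantage depends on the effect outlasting the programme, at least in part.

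The m-GLTEQ point holds only as a matter of interpretation: week-12 totals can contain session time, by an amount the article does not allow one to determine. It calls for a sensitivity analysis, not a change of outcome.

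Both measures are secondary. This is an inexpensive improvement and does not threaten the primary result.

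**What to change.** **BRIEF-2.**
- Name week 24 versus week 0 as the main contrast, since its window covers essentially only time after baseline. Week 52 can serve for maintenance.
- Label the week-12 change descriptive, give the overlap as the reason, and state that a null week-12 result will not be read as absence of a cognitive effect. Apply the same rule to individual trajectories.

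This uses visits already in the schedule. It costs the week-12 cognition claim. The week-24 window also mixes about 12 programme weeks with about 12 weeks after it, so a short-lived effect would still be diluted; the report should say so.

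**m-GLTEQ.**
- Keep total activity as the reported outcome, and state whether respondents were told to count the sessions.
- Add a sensitivity analysis that removes logged session time where respondents counted it. Where that is unknown, show the total with none and with all of the logged time removed, as a range.
- Do not read a fall from week 12 to week 24 as loss of maintained activity without that check.

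The article says that attendance is tracked and that session components are logged. It does not say that minutes by intensity are, so a MET-weighted version may need an assumed weight, for example 3 and 5 side by side. The cost is analysis wording and one additional table.

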##### Assessments of Physical Function (Week 0, Week 12, Week 24, and Week 52)

Each physical assessment is conducted by 2 trained exercise professionals via videoconference at the participant’s convenience, with a caregiver present. The assessments were selected based on their prior use with pediatric patients with cancer in person and for pragmatic reasons related to the feasibility of videoconference delivery [100].

*Aerobic endurance* at weeks 0, 12, 24, and 52 is assessed using the 2-minute step test [101]. Participants position themselves perpendicular to the camera, with their right leg facing the camera, and march in place for 2 minutes. They are instructed to lift their knees to hip height, so that their thighs are parallel to the floor. Assessors count the number of steps completed with the right leg (ie, the leg facing the camera). Participants also report their perceived exertion on a scale from 0 (nothing at all) to 10 (very, very hard; maximal; extremely strenuous exercise) [101]. A greater number of steps indicates higher aerobic endurance. Although this test has not previously been used with pediatric participants with cancer, it has been validated in young adults and adults living with and beyond cancer [52,53,83] and was deemed suitable due to the ease of videoconference administration.

*Lower body flexibility* at weeks 0, 12, 24, and 52 is assessed using the sit-and-reach test [102]. Participants begin by sitting on the edge of their chair and stretching each leg twice for 20 seconds. Next, they position the chair perpendicular to the camera, sit on the edge, and extend 1 leg at a time, keeping the ankle bent at 90°. Participants then hold a measuring device (eg, ruler or measuring tape) with both hands and lean forward as far as possible, reaching toward the toes of the extended leg while keeping the leg straight. Participants hold the maximum flexion position for 3 seconds, then measure the distance from the measuring device to the tip of their toes, recording the measurement to the nearest 0.5 cm. The test is performed twice on each leg, and the best score for each leg is recorded. Higher scores indicate greater lower-body flexibility. The sit-and-reach test has previously been used to assess flexibility among pediatric participants with cancer in person 108,109.

*Shoulder flexion range of motion* at weeks 0, 12, 24, and 52 is assessed using the shoulder flexion test [103,104]. Participants position their chair perpendicular to the camera, sit upright with feet flat on the floor, and face forward so that the shoulder being assessed is perpendicular to the camera. The camera is adjusted to capture the area from the participant’s belly button up to the height their hand would reach when extended overhead. Participants begin with their arms at their sides, palms facing inward (toward the hips), and thumbs pointing upward (toward the ceiling). While keeping the arm straight, participants raise it in forward flexion within the sagittal plane, avoiding compensatory movements (eg, arching the back or moving the arm away from the ear). Once the participant reaches their full range of motion, they hold the position while the assessor takes a screenshot. This procedure is repeated twice for each arm, and the average of both trials is calculated. After the assessment, the assessor measures the range of motion in degrees using a goniometer and anatomical landmarks (head of the humerus, midline of the humerus, and mid-axillary line). Higher scores indicate a greater range of motion. Although this test has not previously been used with pediatric participants with cancer, it has been validated in young adults and adults living with and beyond cancer [52,53,83] and was deemed suitable for videoconference administration.

*Balance* at weeks 0, 12, 24, and 52 is assessed using the flamingo balance test [105]. Participants stand barefoot with their arms crossed over their chest, placing each hand on the opposite shoulder. When ready, the assessor instructs the participant to stand on a leg of their choice while lifting the opposite leg, bending the knee so that the foot is behind them and not touching the standing leg. Timing begins when the foot is lifted and continues for a maximum of 45 seconds or until the participant loses balance. If balance is lost within the first 3 seconds, a second trial may be completed, with the better time recorded. The test is performed once on each leg unless a second trial is required. Longer times indicate better balance. The flamingo balance test has previously been used to assess balance among pediatric participants with cancer in person [106].

*Functional mobility* at weeks 0, 12, 24, and 52 is assessed using the 30-second sit-to-stand test [105] and the timed up and go test [107]. For the 30-second sit-to-stand test, participants sit on a chair with their arms crossed over their chest, hands on opposite shoulders. From this position, participants rise to a full standing position (knees straight) and return to a seated position, ensuring full contact with the seat before standing again. When the assessor says “ready-set-go,” participants complete as many sit-to-stand repetitions as possible within 30 seconds, and the total number is recorded. This test is completed only once. Higher scores indicate greater functional mobility. The 30-second sit-to-stand test has previously been used to assess functional mobility among pediatric participants with cancer in person [69,108-110]. The timed up and go test [107] is also used in this trial to assess functional mobility. Participants, with the help of their caregivers, set up a chair and measure 3 m (10 feet) from the chair, marking the distance with an object or piece of tape. Participants sit with their backs against the chair. On the “ready-set-go” cue, they stand up without assistance, walk as quickly as possible (without running) past the 3-m mark, turn around, and return to the chair. The assessor stops the timer once the participant’s back touches the back of the chair. Participants complete 1 practice trial, followed by 2 counted trials, the results of which are averaged. Lower times indicate greater functional mobility. The timed up and go test has previously been used to assess functional mobility among pediatric participants with cancer in person [106,111,112].

